### Anesthesia Depth

The Bispectral index (BIS) measures anesthesia depth. BIS values can range from 0 to 100 where lower values correspond to deeper anesthesia. Due to the lack of explicit monitoring results, three trials investigated the effect of BIS monitoring on postoperative NCD incidence^2-4^. Ballard et al. showed that EEG and cerebral oximetry monitoring reduced the rate of mild neurocognitive disorders at 1 week and 3 months after surgery compared with routine care^2^. There was no effect on severe NCD but the study sample was low (72 patients total). The CODA trial compared 921 patients randomly assigned to receive BIS-guided anesthesia or routine care^3^. Patients in the routine care group had a higher rate of NCD at 3 months than BIS-guided patients. This higher rate of NCD was associated with lower BIS, longer duration of BIS < 40 and higher anesthetic dose administered in the routine care group. No difference in the rate of NCD at 1 week was observed among groups. Radtke et al. studied more than 1100 patients randomly allocated to have BIS monitoring versus standard of care^4^. The rate of NCD at 1 week and 3 months (explored as secondary endpoints) were not different between groups. But, in contrast to CODA, mean BIS values were similar in the BIS and control groups.

Nevertheless, these three previous studies had strong limitations: blood pressure management data were unavailable (low blood pressure during surgery may clearly be a cofounding factor for NCD^36,37^) and nociception levels were never monitored, ignoring the effect intraoperative large doses of opioids or intraoperative excess of nociception might also have on postoperative NCD. Finally, results were unclear if reduction in perioperative NCD incidence was related to avoidance of burst suppression – an electroencephalographic pattern suggesting excessively deep anesthesia^38^.

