# Study Objectives

## Primary Objective

The main objective of the study is to investigate whether EEG-guided anesthesia – intended to reduce anesthetic administration and minimize burst suppression during general anesthesia – **decreases the incidence of NCD at postoperative day 1 in elderly patients (> 70 years old)** undergoing major (expected duration > 1h) non-cardiac surgery compared to standard of care (SOC, BIS installed but not used to guide anesthesia).

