## Secondary Objectives

Secondary objectives are to investigate the effect of EEG-guided anesthesia on:

- neurocognitive disorders (NCDs) at postoperative day 2, 7, 15, 30 and 90,
- patients’ perioperative cognitive trajectories,
- postoperative delirium,
- intraoperative consumption of volatile anesthetics, opioids and vasopressors,
- intraoperative hypotension (number of interventions to treat hypotensive events),
- cerebral hypoxemia (assessed by cerebral oximetry),
- cumulative burst suppression duration and cumulative low processed EEG (BIS) values duration during anesthesia,
- risk of awareness,
- postoperative quality of life / recovery outcomes (including length of hospital stay and surgical complications).

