## Anesthesia Protocol

### General

All patients will undergo general anesthesia with the following: induction with IV slow boluses of lidocaine to numb the vein, propofol 1.5mg.kg^-1^, remifentanil 1µg.kg^-1^ over 30 seconds, rocuronium 0.8 mg.kg^-1^. We will proceed to orotracheal intubation when response to neuromuscular stimulation of the adductor pollicis has reached 5% of the original T4 amplitude. The maintenance of anesthesia will depend on sevoflurane to reach [0.8–1.2] minimal alveolar concentration (MAC; MAC adjusted to the patient’s age) in the control group, and to achieve a BIS of [40-60] in the EEG-guided group (see below). The remifentanil infusion will start at 0.02 µg.kg^-1^.min^-1^ and increase by 0.02 µg.kg^-1^.min^-1^. If the NOL index is > 25 for more than 1 min, we will administer one bolus of 0.3 µg.kg^-1^. The maximum remifentanil rate allowed intraoperatively will be 0.3 µg.kg^-1^.min^-1^. This rate will be decreased by step of 0.02 µg.kg^-1^.min^-1^ if the NOL index is < 5 for more than 3 minutes (for a minimum rate of 0.02 µg.kg^-1^.min^-1^). We will administer intravenous boluses of rocuronium as needed for the response to TOF stimulation to stay below 2/4.

Baseline mean arterial blood pressure (MAP) will be defined as the average of 3 consecutive values taken 1 min apart and determined before the induction of general anesthesia. Intravenous (IV) infusion of phenylephrine will start at 0.2 µg.kg^-1^.min^-1^ and adjusted to maintain +/- 20% of the baseline values of the pre-anesthesia MAP. Benzodiazepines or ketamine will not be used, and patients will receive standard prophylaxis against postoperative nausea and vomiting (avoiding haloperidol).

Remifentanil and phenylephrine infusions will be discontinued when the skin is closed. At the same time, muscle relaxation will be antagonized using neostigmine 0.04 mg.kg^-1^ and glycopyrrolate 0.01 mg.kg^-1^, and bolus of ondansetron 4mg and hydromorphone 0.006 µg.kg^-1^ administered. Sevoflurane will be discontinued when the wound dressing is completed, and patients will be extubated in the operating room, then transferred to the post-anesthesia care unit (PACU).

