### Monitoring

Routine monitoring of patients will be the same for both groups and will include 5 leads ECG, non-invasive blood pressure, pulse-oximetry and a temperature probe. We will record all data using the Dräger Perseus A500 (Dräger Medical, Lübeck, Germany) monitor and send all anesthesia related data electronically to a research computer for anonymized storage and further analysis.

We will place the NOL index finger probe (PMD-200™ device, Medasense Biometrics Ltd, Ramat Gan, Israel) and the bilateral cerebral regional oximetry rSO_2_ (Invos™, Medtronic, Canada) (both are available to the anesthesiologist for both groups throughout the entire anesthesia).

Bilateral BIS^TM^ EEG sensor (Medtronic, Canada) will be placed on the forehead for all patients. For the SOC (standard of care) group, only the electrode status display will be available; the rest of the data will be hidden by a dark screen – and unavailable to the anesthesiologist during the anesthesia.

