### Intervention

In the EEG-guided group, the information provided by the BIS^TM^ monitor will guide the volatile anesthetic administration in the EEG-guided group. Sevoflurane end-tidal anesthetic concentration (ETAC) will be adjusted to maintain a BIS value between 40 and 60, a Suppression Ratio (SR; % of time with suppressed brain electrical activity) at 0%, a direct EEG display without any suppression time and a spectrogram (DSA or density spectral array) with most of the EEG wave frequency within the Alpha (8-12Hz), Theta (4-8Hz) and Delta (0.5-4Hz) frequencies.

In the non-EEG-guided group, the MAC of sevoflurane (adjusted to age) will be used to guide the intraoperative anesthesia delivery and MAC will be kept between 0.8 and 1.2.

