#### Secondary Endpoints

- The incidence of major NCD at postoperative day 2, 7, 15, 30 and 90
- The evolution over time in cognitive assessment scores defining cognitive trajectories,
- The incidence of postoperative delirium during hospital stay,
- The total intraoperative consumption of volatile anesthetics, opioids and vasopressors over surgery time
- The incidence of intraoperative hypotension,
- The incidence of cerebral hypoxemia,
- The cumulative burst suppression duration and low BIS values duration during anesthesia,
- The incidence of awareness,
- The difference between quality of recovery scores between groups.

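### Sevoflurane exposure is measured as volatile consumption over surgery time, which depends on gas flow, has an unclear time base and is not what either arm titrates

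*Protocol*

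**What the plan says.** The Primary Objective (C.1) describes EEG guidance as "intended to reduce anesthetic administration and minimize burst suppression during general anesthesia". The Secondary Objectives (C.2) list "intraoperative consumption of volatile anesthetics, opioids and vasopressors" without unit, method or period. The Secondary Endpoints (D.6.3.2, and the same item in the protocol summary) add a period: "The total intraoperative consumption of volatile anesthetics, opioids and vasopressors over surgery time".

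The arms are steered on other quantities. In the EEG-guided arm, "Sevoflurane end-tidal anesthetic concentration (ETAC) will be adjusted to maintain a BIS value between 40 and 60" (D.4.3). In the control arm, age-adjusted MAC is held between 0.8 and 1.2.

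On timing, D.4.1 states: "Sevoflurane will be discontinued when the wound dressing is completed". The remifentanil and phenylephrine infusions stop earlier, at skin closure. The EEG endpoints in the same list have a different period: "The cumulative burst suppression duration and low BIS values duration during anesthesia".

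On data capture, the workstation record is kept, and the team will "send all anesthesia related data electronically to a research computer" (D.4.2). No listed endpoint is end-tidal concentration, MAC or MAC-time, and fresh gas flow is not mentioned anywhere.

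**The concern.** A trial of titration has to show that the titrated exposure differed between arms. The protocol reads earlier work this way. In B.1.4 it explains one trial's result partly by higher anesthetic dose and lower BIS under routine care. Of another trial, which found no difference in cognitive disorders, it remarks that "mean BIS values were similar in the BIS and control groups". Readers will ask the same of this trial, whether the primary result is positive or null.

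For the drug side of that question the protocol offers only consumption. Three features make it a poor choice:

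- The amount of agent used reflects the gas flow as well as the concentration reaching the patient. The flow is left to an anesthesiologist who has opened the allocation envelope (D.5).
- Consumption is not the quantity that defines either arm.
- The word *over* can mean accumulated during surgery or divided by surgery time. On either reading the period is not the one in which sevoflurane is given.

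At stake is the interpretation of one secondary endpoint, and through it how firmly a primary result can be tied to reduced anesthetic dose.

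**Working it through.** **The plan's own figure.** The protocol gives no number for the consumption endpoint. Its sample size for the primary endpoint (G.1: 15% versus 5%, two-sided 0.05, 80% power) does reproduce. With pooled variance and no continuity correction,

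n per arm = [1.960·√(2·0.10·0.90) + 0.842·√(0.15·0.85 + 0.05·0.95)]² / 0.10² = (0.8315 + 0.3521)² / 0.01 ≈ 140.1, rounded up to 141.

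That gives 282 in total, and 282/0.9 = 313.3, rounded up to 314. With 141 per arm a continuous endpoint has about 80% power for a difference of 0.335 SD. The number of patients is therefore not the obstacle; the measure is.

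**Quantity measured against quantity titrated.**

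| | EEG-guided arm | Control arm | Endpoint |
|---|---|---|---|
| Variable | end-tidal sevoflurane, steered by BIS | age-adjusted MAC | total agent consumed |
| Depends on gas flow? | no, read directly | no, read directly | yes |

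**Effect of flow** (illustration; the protocol gives no flows). Assume consumption ≈ flow × delivered concentration × time. At an assumed 1.5% for one hour:

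- 0.5 L/min: 500 × 0.015 × 60 = 450 mL vapour
- 1 L/min: 900 mL
- 2 L/min: 1800 mL
- 4 L/min: 3600 mL

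This is an 8-fold range at one concentration. A 20% lower concentration in the EEG-guided arm is fully offset by a flow 1/0.8 = 1.25 times as high. If flows have the same distribution in both arms, they only add variance to the comparison planned in G.2.3 (t-test or Mann-Whitney-Wilcoxon). If they differ by arm, the comparison is biased.

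**Effect of the time base** (illustration; the protocol gives no durations and does not define surgery time, taken here as ending at skin closure). Under the divided-by reading, and if sevoflurane runs X minutes longer than surgery of S minutes, the rate is inflated by (S + X)/S:

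| S (min) | X = 15 | X = 60 |
|---|---|---|
| 60 | 1.25 | 2.00 |
| 120 | 1.125 | 1.50 |
| 180 | 1.08 | 1.33 |

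The factor is largest in short cases. It acts on patients in both arms, so under 1:1 randomisation it is expected to be largely common to them. It adds noise and dependence on case mix rather than a shift in one direction. Under the accumulated-during reading there is no such factor, but sevoflurane given outside surgery time is not counted.

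**BIS durations.** These endpoints do state a period, the anesthetic. Cumulative minutes still scale with case length: an assumed 5% suppression burden is 0.05 × 75 = 3.75 min in a 75-minute case and 0.05 × 300 = 15 min in a 300-minute case. This contrasts two patients, not two arms.

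**The case against.** A reader might infer that the trial cannot show reduced sevoflurane exposure at all. The documents do not support that. End-tidal concentration is the titrated variable, the workstation data are stored electronically (D.4.2, E.1), BIS is recorded in both arms, and burst suppression and low-BIS time are listed endpoints. In the earlier trial cited in B.1.4, lack of separation was itself shown by BIS, and that route is open here. What remains is narrower: separation in depth is covered, separation in drug exposure is not well covered. An end-tidal measure chosen after the data are seen is weaker than one fixed in advance.

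The bias from gas flow is hypothetical. D.1 says the rest of the anesthetic is to be alike in both arms, and nothing suggests that flows will differ. This stands, and is why the conclusion says noisy, and biased only if flows differ. D.1 does not, however, set any flow.

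The inflation factors need one reading of *over*, and the word *total* favours the other. This also stands. The mismatch at the end of the case applies to sevoflurane alone, since the two infusions stop at skin closure.

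A reader might go on to rescale opioid and vasopressor doses by infusion time. That would be a step back: the intervention may itself shorten the infusion, and a dose per infusion minute could then hide a real fall in total use.

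Finally, unit and derivation can be left to a SAP, which is not shown. That answers the missing unit. It does not answer the choice of consumption over surgery time, which the protocol itself makes.

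**Conclusion.** The concern holds in limited form. The sole listed measure of sevoflurane exposure depends on an unstandardised gas flow, differs from the quantity titrated in both arms, and carries an ambiguous period that does not match sevoflurane delivery. It is a noisy test of whether EEG guidance reduced anesthetic administration, and a biased one if flows differ by arm. Under the simple product model a 1.25-fold difference in flow is enough to mask a 20% difference in concentration; the flows, concentration and durations used here are assumptions. The primary endpoint, its test and the sample size are untouched, and separation in depth can be read from the BIS endpoints. This is a worthwhile and cheap improvement to a secondary endpoint, not a flaw that threatens the trial.

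**What to change.** Define the volatile-exposure endpoint in D.6.3.2 and the protocol summary as the time-weighted mean age-adjusted end-tidal MAC from start to discontinuation of sevoflurane, taken from the recorded workstation data. Confirm first that end-tidal concentration is among the exported variables, since no passage names it explicitly. Keep volatile consumption as a descriptive measure, with its unit and period stated. Leave opioid and vasopressor totals undivided by infusion time, and say which meaning of *over* applies to them. Optionally, report burst suppression and low BIS also as a percent of anesthesia time beside the cumulative minutes.

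The change is to endpoint wording. It alters no treatment, visit or sample size, and costs some extra processing of data that the protocol already plans to record.

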#### Tertiary endpoints

- Incidence of major NCD at postoperative day among the following subgroups of patients: different surgical types and duration, patients with preoperative neurocognitive disorder (defined as a preoperative MoCA score < 26 ^46^), frail patients (defined as a CFS ≥ 5 ^59^), depressive patients (defined as a PHQ-9 score ≥ 10 ^60^) and patients above 80 years old.

# Subject Visits

## Data Collection Procedures

We will collect all electronic data from the medical monitoring including BIS^TM^ and PMD-200^TM^. Monitor times will be synchronized before any data is collected. We will note on a separate Case Report Form (CRF) and in the integrated system of PMD-200^TM^, all anesthesia and surgery related events. At the end of anesthesia, and once the patient is extubated, we will export all electronic data. Data will be anonymized and stored in a dedicated research computer at the Department of Anesthesiology and Pain Medicine of HMR-CEMTL.

## Safety and Adverse Events

Research personnel and hospital staff will make all efforts to ensure the safety of the participants. We expect no adverse events resulting from this research.

### Anesthesia Management Protocol

The anesthetic management in the proposed study represents a standard and conventional approach to general anesthesia (see “Risks” section below). There is no additional anesthesia-related patient risk arising from participation in this study.

### Cognitive Assessment

During recruitment, we will explain to all patients that participation in the study is voluntary, non-binding, and that cognitive assessment performance has no bearing on medical treatment. The cognitive tests used in the proposed study will require the participant to verbally interact with the examiner and, for a few tasks, write words or draw images – the risk of physical harm from testing is minimal or not existing. We will schedule (to the best of our ability) postoperative testing when patients are awake, comfortable, and not slated for any treatments (dressing changes, physiotherapy, etc.).

### Medical Monitoring

The PI will review all data, including completeness of study data, enrolment, protocol deviations, dropouts, adverse events on a regular basis (weekly or bi-weekly) and an annual report of all adverse events. A summary of the investigation will be submitted to the approving Internal Review Board (IRB).

### Definition of Adverse Events

There are no anticipated adverse events for this research. If adverse events occur, the PI research personnel will report it to the approving IRB. Adverse events will be graded as: Mild, Moderate, or Serious; and Related, Possibly Related, or Not Related to study procedures.

Adverse Event: Any unfavorable and unintended sign, symptom or disease temporarily associated with the use of a medical treatment or procedure.

Serious Adverse Event: Any adverse event that results in any of the following outcomes:

- Death
- Outpatient hospitalization or prolongation of existing hospitalization
- Persistent or significant disability/incapacity.

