## Research plan and timeline

Patients will be screened at the preoperative clinic. The day of the surgery (D0), after signing the consent form, patients will undergo the inclusion visit. Cognitive assessment will be performed using the MoCA and verbal fluency tests by a trained research team. Patients will also be screened for depression and frailty. The patient will then be randomized in the EEG-guided or SOC group.

Postoperative visit will be performed at postoperative days 1 and 2 (D1 and D2). Cognitive assessments will be performed using MoCA and verbal fluency tests. Patients will also be screened for postoperative delirium.

Once patients return home, phone interviews will be done at D7, D15, D30 and D90. Cognitive assessments will be performed using the telephone version of the MoCA (T-MoCA) and verbal fluency tests. Quality of recovery will be evaluated at D30 and D90 using the QoR-15 questionnaire.

T-MoCA and T-MoCA part of the MoCA as well as verbal fluency will be used to establish cognitive trajectories of the two groups.

The 3 versions of the MoCA will be alternately and randomly used to limit learning effect.

Estimated time for each visit is approximatively 45 minutes. The study timeline used tests and expected cognitive trajectories are presented in figure 1.

All the tests are provided in the references and detailed below. These tests are also attached in the annexes in French and in English.

[figure not shown]

**Figure 1. Study timeline, tests and expected cognitive trajectories**. *MoCA: Montréal Cognitive Assessment; PHQ-9: Patient Health Questionnaire 9; CFS: Clinical Frailty Scale; EEG: electroencephalograph; SOC: Standard of Care; CAM: Confusion Assessment Method; QoR: Quality of Recovery; T-MoCA: Telephone MoCA.*

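### The only definition of a serious adverse event has a garbled hospitalization criterion, no life-threatening criterion, and a grading scale that merges severity with seriousness

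*Protocol*

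**What the plan says.** Definition of Adverse Events (E.2.4) holds the whole rule. It opens the list with "Serious Adverse Event: Any adverse event that results in any of the following outcomes" and gives three outcomes: death; "Outpatient hospitalization or prolongation of existing hospitalization"; and "Persistent or significant disability/incapacity". The list ends there.

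The same section sets the grading: "Adverse events will be graded as: Mild, Moderate, or Serious; and Related, Possibly Related, or Not Related to study procedures".

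On reporting, it says: "If adverse events occur, the PI research personnel will report it to the approving IRB". Medical Monitoring (E.2.3) adds weekly or bi-weekly review by the PI and "an annual report of all adverse events". Neither statement is limited to serious events.

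**The concern.** Seriousness is decided from this text, and three features make it an unreliable guide.

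- The hospitalization criterion contradicts itself in its first half, and its second half covers only a stay already under way.
- An event that threatens life but leads to none of the three outcomes is not serious.
- One word carries two meanings, so it is unclear whether an assessor should rate how intense an event was or what it led to.

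The population makes this worth correcting. Patients are 70 or older and have major surgery, and follow-up runs well past discharge: "Once patients return home, phone interviews will be done at D7, D15, D30 and D90". Readmission is therefore a natural event type over most of follow-up. Delirium Assessment (D.6.2.2) itself foresees patients still ventilated in intensive care after surgery. What is at stake is whether two assessors would class the same event alike.

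**Working it through.** No arithmetic applies: the plan states no figure on this point and the defect is one of wording. The check applies the rule as written to typical events and then looks for a correction elsewhere.

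**Step 1. The outcome list applied to three events.**

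| Event | Death | Hospitalization item | Disability item | Class |
|---|---|---|---|---|
| New inpatient admission after discharge, full recovery | No | Literally no: not outpatient, and no current stay to lengthen. Yes if the slip is read as inpatient | No | Depends on the reader |
| Life-threatening event during surgery, resolved, discharge on the expected day | No | No, on either reading | No | Not serious |
| Life-threatening event on the ward, longer stay | No | Yes | Not needed | Serious |

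The first row turns on how the slip is read. The second does not: no sensible reading of the list makes that event serious. The third shows that many life-threatening events still qualify by another route, so the gap is narrow.

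**Step 2. The grading scale.** The text "Adverse events will be graded as: Mild, Moderate, or Serious" can be read in two ways.

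- *One scale, with its top level defined by the outcome list.* An event that lengthens the stay is graded Serious, once. An intense event with none of the listed outcomes must be Mild or Moderate. The scale is coherent, but it does not record intensity separately.
- *An intensity scale, with a separate outcome definition below it.* An intense event with none of the outcomes is Serious by grade but not by definition. A slight event that lengthens the stay is Mild by grade but serious by definition.

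The section does not say which is meant. Either way, severity and seriousness are not recorded as two separate facts.

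**Step 3. Other safety text.** The Adverse Events entry in the protocol summary, Safety and Adverse Events (E.2), Anesthesia Management Protocol (E.2.1) and Risks (F.3) say that no adverse events, or little added risk, are expected. Medical Monitoring (E.2.3) describes review and reporting. None supplies another definition, a life-threatening criterion or a separate severity grade.

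**Step 4. What depends on the label.** Reporting to the IRB covers all adverse events. The protocol states no separate reporting timeline for serious events. Its Endpoints section (D.6.3) lists no serious-event endpoint, and its Statistical Methods (G.2) plan no comparison of serious events. The direct effect is therefore on how events are classified and described.

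**The case against.** The strongest case against is that little follows from the wording. The hospitalization slip is obvious, and staff would probably read it as admission. It could even be taken to mean admitting someone who is by then an outpatient, which is a readmission. Most life-threatening events after major surgery would qualify through death, a longer stay, disability or admission. The grading can be read as one coherent scale. Length of stay and surgical complications are named in Secondary Objectives (C.2) regardless of the label. All of this limits the size of the point and stands.

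It does not remove the point. An operative definition should not depend on readers mending it, and the missing life-threatening criterion and the double use of Serious remain once the slip is read charitably.

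Four stronger inferences are tempting, and the protocol does not support them:

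- *Reports to the IRB would be incomplete.* The reporting text covers every adverse event; only the label could be wrong.
- *Serious-event counts by arm would be distorted.* The protocol plans no such comparison.
- *A slight event that lengthens the stay necessarily receives two grades.* That follows only on the second reading in Step 2.
- *A definite number of readmissions would be lost.* The protocol gives no readmission rate, and any count also assumes that every assessor applies the slip literally.

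**Conclusion.** The definition is wrong as written, and the point is minor. The consequence is misclassification of seriousness, not failure to report. It falls mainly on life-threatening events that resolve without a longer stay or lasting disability. Readmissions are affected only if the slip is taken at its word. The primary endpoint, the sample size and the analyses planned in the protocol are untouched.

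The number of events affected cannot be derived from the protocol, and none is claimed. The conclusion rests on two assumptions: that the outcome list is meant to be complete, as its lead-in indicates, and that no separate safety document, which the protocol does not mention, replaces it.

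**What to change.** In Definition of Adverse Events (E.2.4):

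1. Replace Outpatient with Inpatient in the hospitalization criterion and leave the rest of that line as it is.
2. Add Life-threatening event to the list of outcomes.
3. Grade severity as Mild, Moderate or Severe.
4. Record seriousness as a separate yes/no item, decided only by the outcome list.

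The cost is a few words in one section, one CRF field, and slightly more events classed as serious. Endpoints, sample size and treatment do not change. If events have already been recorded, those with enough detail on file can be reclassified under the corrected definition.
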